**Figure 1 figure1:**
[figure not shown]
Three screenshots from the interactive dashboard. Left: Each week participants are asked to assess their current consumption. Middle: One of the modules explores normative comparison of consumption levels. Right: Participants can see their consumption over time, allowing them to compare with their own goals.

### Design

To study the effect of the intervention, a 2-arm parallel group randomized controlled trial will be employed. Nested within this trial will be the 3 substudies.

#### Recruitment and Eligibility

Using Web search engine advertisements (Google, Yahoo, and Bing) and social media (Facebook), we will target individuals in the general population of Sweden seeking help to reduce their alcohol consumption (advertisements are shown in Figure 2). Participants will initially be recruited over a 6-month period. Additional 6-month periods will be added if not enough participants have been recruited according to the initial power calculation. If 20.03% (426/2126) or less of the required population has been recruited at 12 months, then recruitment will stop at this time and data will be analyzed to inform future trial design. Recruitment will stop after 24 months if not before.

Individuals interested in participating in the study will be asked to send an SMS message with a specific code to a dedicated phone number. Within 10 min, participants will receive an SMS with a hyperlink that takes them to a Web page asking for informed consent. Individuals will be randomized to 1 of 2 different means of presenting the trial procedure when asking for informed consent (Consent-1 and Consent-2). Please see Multimedia Appendix 1 for more details.

All individuals giving informed consent will be asked to complete a baseline questionnaire, which will also assess eligibility for the trial. The inclusion criteria will include the following: aged 18 years or older, ownership of a mobile phone, and being classified as a risky drinker according to Swedish guidelines.

Note that there is no upper limit to alcohol consumption as an exclusion criterion, meaning the study population is anticipated to comprise both harmful (ie, individuals who have experienced harm from any level of consumption [48]) and hazardous drinkers (ie, individuals with a consumption pattern that suggests increased risk to health [48]). No additional support will be offered to individuals who have a very high-consuming behavior.

#### Intervention and Control Conditions

Eligible individuals will be randomized to either an intervention group or a control group (intervention and control). The intervention group will receive the novel intervention for 4 months and will also be recommended to read about alcohol, health, and society on the same website as the control group (see Multimedia Appendix 2). Participants allocated to the control group will be advised that they will go through an initial phase of 4 months during which they are to receive information to increase their motivation and reduce their consumption, after which they will be given access to the new support tool. Thus, individuals allocated to the control setting will be given access to the novel intervention after completion of the final follow-up (4 months after randomization); no further data will be collected from individuals in the control setting.

**Figure 2 figure2:**
[figure not shown]
Advertisements shown in search and on Facebook.

The control group will be randomized further into 2 groups (Info-1 and Info-2). Both Info-1 and Info-2 will receive a single SMS message with basic health information regarding short- and long-term effects of alcohol consumption. In this substudy, we incorporate a contrast between 2 very brief types of information; one which emphasizes possible complexities associated with the short- and long-term effects of alcohol (such as is widely available from alcohol industry sources [49], Info-1) and another which provides a clear and straightforward public health messaging style (while being appropriately evidence informed, Info-2). Each is delivered in a single SMS and includes the same link to a Swedish website with information about alcohol and society (IQ). As individuals who have enrolled are looking for help to change their alcohol consumption, we anticipate that most participants will be motivated to click on the link. It is plausible that either type of message could encourage trial participants more than the other to click on the link. This exploratory substudy concerned with the direct behavioral effects on accessing health information will assist further consideration of the design of control conditions and be relevant to alcohol health promotion more broadly. As there is some health information provided, including to participants who do not click on the link, we refer to the control condition as alcohol information. Please see Multimedia Appendix 2 for more details.

#### Mediation

To further understand the potential effects of the proposed intervention, we will measure psychosocial factors believed to be important for behavior change. We will use these measures to estimate how the effects of the intervention are mediated through these factors. Specifically, we will measure perceived confidence, importance, and know-how.

Confidence is closely linked to self-efficacy, a cornerstone of modern theoretical models of behavior change, prominently in social cognitive theory [50]. Importance is an aspect of both motivation and intention, 2 key factors in modern theory, for example, protection motivation theory [51], social cognitive theory [50], and theory of planned behavior [52] (and has been retrospectively added to the health belief model [53]). Know-how, alternatively expertise or skills, connects with several factors in theoretical models, for example, to behavioral control in the theory of planned behavior, and has been proposed as a specific necessary factor for behavior change [43,54]. Measuring if, and to what degree, these factors mediate the effect of the proposed intervention will help us better understand which factors are affected by the intervention and thus, why the intervention (potentially) works.

#### Randomization

In all cases, randomization will be fully computerized, will not employ any strata or blocks, and will not be possible to subvert as this and all subsequent study processes are fully automated. The main study will be single-blind as participants will be aware that 2 settings exist, and they will know which one of them they have been allocated to (intervention or control). The substudies involving Consent-1, Consent-2, Info-1, and Info-2 will be double-blind as participants will not be aware of the existence of the substudy or that they have been randomized. It is not possible to blind the individual responsible for data analysis, as this individual will also be responsible for data collection and involved in the monitoring of the technical platform.

#### Follow-Up

At 1 month after randomization, an SMS message will be sent to both intervention and control with a hyperlink to a questionnaire exploring mediators. At 2 and 4 months after randomization, an SMS message will be sent to both intervention and control with a hyperlink to a questionnaire exploring alcohol consumption. At 2 months after randomization, the questionnaire exploring recall of trial procedures will be added for both groups. At 4 months after randomization, the intervention group will receive questions regarding the usability and their experiences of the intervention, and the control group will receive questions regarding their experiences of being allocated to the control condition.

Figures 3 and 4 offer an overview of the design in the form of a Standard Protocol Items: Recommendations for Interventional Trials figure and Consolidated Standards of Reporting Trials flowchart.

### Hypotheses

There are 5 main and 2 exploratory hypotheses mentioned in Textbox 1.

Apart from the hypotheses tested here, we will also do both a quantitative and qualitative analysis of users’ experiences of engaging with the intervention and being allocated to the control group.

### Measures

All questions asked at baseline and subsequent follow-ups can be found in Multimedia Appendix 3.

For hypotheses 1, 6, and 7:

Primary outcome measures: Total weekly alcohol consumption and frequency of heavy episodic drinking.Secondary outcome measures: Classification as risky drinker according to Swedish guidelines.

For hypothesis 2:

Mediation measures: Confidence in one’s ability to reduce consumption, importance of reducing, and knowledge of how to reduce consumption.

For hypotheses 3 and 4:

Primary outcome measures: Enrollment rates from each study conditionSecondary outcome measures: Recall of trial procedures measured through a series of questions.

For hypothesis 5:

Primary outcome measures: Rates of additional information being requested by pressing on the supplied hyperlink.

**Figure 3 figure3:**
[figure not shown]
Standard Protocol Items: Recommendations for Interventional Trials figure.

Total weekly alcohol consumption will be assessed by asking participants the number of standard units of alcohol they consumed last week, that is, a short-term recall method [55]. Using a summary measure, rather than asking day-by-day, will allow for the same question to be asked, regardless if responses are collected via Web questionnaires, SMS, or by phone interviews (see Follow-up Attempts). In addition, 1 study suggests that when considering short-time spans, summary measures do not imply any noteworthy bias compared with asking for consumption day-by-day [56]. The frequency of heavy episodic drinking will be assessed by asking participants how many times they have consumed more than 4 (females) or 5 (males) standard units of alcohol on 1 occasion the past month, again asking for a summary measure over a concrete time period. An individual is classified as a risky drinker if either total weekly consumption or heavy episodic drinking exceeds recommendations.

Confidence, importance, and know-how will be measured at baseline and at 1-month follow-up by asking “How confident are you that you will be able to reduce your alcohol consumption?,” “How important do you think it is to reduce your alcohol consumption?,” and “How well do you know how to reduce your alcohol consumption?,” all 3 with response options on a 10-point scale (see Multimedia Appendix 3). The wording of the questions at 2- and 4-month follow-up will change to include those who have reduced their consumption: “How confident are you that you will be able to reduce or keep a lower level of alcohol consumption?,” “How important do you think it is to reduce or keep a lower level of alcohol consumption?,” and “How well do you know how to reduce or keep a lower level of alcohol consumption?.”

**Figure 4 figure4:**
[figure not shown]
Consolidated Standards of Reporting Trials flow diagram (see power calculation section for details of n).

Hypotheses.
**Main Hypotheses**
1. Alcohol consumption will differ between intervention and control groups, with the intervention group drinking less than control at 2 and 4 months after randomization. The 2-month interval will be primary.2. Confidence, importance, and know-how at 1-month follow-up will mediate the effects of the intervention on drinking outcomes at 2-month follow-up. The same measures at 2-month follow-up will mediate the effect on drinking outcomes at 4-month follow-up.3. Enrollment rates will differ between groups Consent-1 and Consent-2.4. Accurate recall of study parameters will differ between groups Consent-1 and Consent-2.5. Rates of accessing further information will differ between groups Info-1 and Info-2.
**Exploratory Hypotheses**
6. Alcohol consumption will differ between groups Consent-1 and Consent-2 at 2 and 4 months after randomization. The 2-month interval will be primary.7. Alcohol consumption will differ between groups Info-1 and Info-2 at 2 and 4 months after randomization. The 2-month interval will be primary.

With regard to recall of trial procedures, there are 3 parameters that are of interest. First, participants will be asked if they recall receiving information about allocation to 2 different groups. As information regarding group allocation was presented identically for Consent-1 and Consent-2, this question will both work as a check that randomization succeeded and as a general baseline for recall regardless of group allocation. Second, participants will be asked if they recall how personal data will be handled in the study and their rights to these data. Finally, participants will be asked if they remember how the data would be analyzed and results communicated (see Multimedia Appendix 3).

We wish to measure if participants access further health-related information after reading a short SMS with basic information about short-term and long-term consequences of alcohol consumption. A proximal outcome of this is to measure whether or not participants in Info-1 and Info-2 request more information by following the included hyperlink. In addition, a short questionnaire at 4-month follow-up will investigate the control group participants, which will be used to investigate further differences between Info-1 and Info-2 (see Multimedia Appendix 3).

The acceptability and usability of the intervention will be measured through a questionnaire and the system usability scale [57] at 4-month follow-up (see Multimedia Appendix 3). The system usability scale comprises 10 Likert items exploring users’ perception on usability of a product or service.

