### Statistical Analysis Methods

All analyses will be done under the intention-to-treat principle, where all randomized individuals will be included. Missing outcome data will initially be handled by a complete-case analysis, which assumes that data are missing at random (MAR). If data are systematically missing, then it may be the case that early responders differ from late responders and, in extension, that late responders are more similar to nonresponders. We will, therefore, explore the plausibility of the MAR assumption by regressing the primary outcomes on the number of follow-up attempts needed before a response was recorded. To further explore the MAR assumption, attrition will be investigated among study groups by comparing baseline characteristics between those who did and did not respond at follow-up. A sensitivity analysis that includes imputed values for missing outcome data (using multiple imputation by chained equations [58]) will also be performed. Data will be graphically examined for outliers or data input errors, and sensitivity analyses will be performed excluding any erroneous data points.

For all models, coefficients of interest will be assessed for statistical significance using a null hypothesis testing approach, where tests will be 2-tailed at the .05 significance level. Alongside the null hypothesis tests, posterior distributions using a Bayesian approach will be calculated for each coefficient. Both significance tests and posterior distributions will create a basis for scientific inference [59].

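### Hypothesis 6 compares drinking by consent mode among enrolled people only, so the statement that every analysis includes all randomized individuals cannot hold for it

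*Protocol article*

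**What the plan says.** The order of events is set out in the protocol article under Recruitment and Eligibility, Intervention and Control Conditions, and Follow-Up:

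- At the consent page: "Individuals will be randomized to 1 of 2 different means of presenting the trial procedure when asking for informed consent".
- After that: "All individuals giving informed consent will be asked to complete a baseline questionnaire, which will also assess eligibility for the trial".
- Only eligible people are then allocated to intervention or control.
- At 2 and 4 months, "an SMS message will be sent to both intervention and control with a hyperlink to a questionnaire exploring alcohol consumption".

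Hypothesis 6 reads "Alcohol consumption will differ between groups Consent-1 and Consent-2 at 2 and 4 months after randomization". The analysis section gives it the same regressions as hypotheses 1 and 7. Both unadjusted and adjusted models are fitted, and the adjusted one is primary. Hypothesis 3, listed as a main hypothesis, expects enrolment to differ between the consent modes.

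Statistical Analysis Methods opens with "All analyses will be done under the intention-to-treat principle, where all randomized individuals will be included". A restriction to consenters is stated only for the adjusted enrolment models, not for hypothesis 6. Ethical Concerns mentions data from people who decline the trial, but the article describes no drinking measure or follow-up for them.

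**The concern.** Hypothesis 6 can be tested only in people selected after the randomization it examines. Randomization makes the two consent groups comparable at the consent page. It does not make those who go on to consent, complete baseline and qualify comparable. The protocol itself expects consent mode to affect who enrols.

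The intention-to-treat sentence covers all analyses. Under it, a significant hypothesis 6 result could be reported as a randomized effect of the consent presentation on drinking. The design supports only a comparison among those who enrolled.

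**Working it through.** **Plan's own figure.** The protocol gives no figure for hypothesis 6. Its main power figure was checked because its distributional inputs are borrowed below: stated 0.79 at N=1800, recomputed 0.7915 by formula and 0.787 by simulated negative binomial regression.

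**Can the all-randomized statement be met?**

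| Allocation | Made | Drinking follow-up planned for all allocated? |
|---|---|---|
| Consent-1 / Consent-2 | before consent, baseline, eligibility | no, enrolled only |
| Intervention / control | after eligibility | yes |
| Info-1 / Info-2 | within the control group | yes |

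Multiple imputation does not close the gap in the first row. It can address enrolled non-responders, but decliners complete no baseline questionnaire from which to impute.

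**When does selection produce a difference?** From the protocol: mean 10 units, negative binomial dispersion 1, about 2126 × 0.85 / 2 ≈ 903 analysed per consent group. Assumed: two-thirds of candidates drink 6 units and one-third drink 18 (mean 10), with no true effect of consent mode. Enrolled mean = (2/3 × pL × 6 + 1/3 × pH × 18) / (2/3 × pL + 1/3 × pH), where pL and pH are the enrolment proportions of lighter and heavier drinkers. Mode 1 enrols 60% of both.

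- Mode 2 enrols 50% of both: mean 10.0, ratio 1.00, rejection 5%. An enrolment difference alone creates no bias.
- Mode 2 enrols 60% and 50%: 5.4 / 0.567 = 9.53, ratio 0.95, unadjusted rejection about 16%.
- Mode 2 enrols 60% and 40%: 4.8 / 0.533 = 9.0, ratio 0.90, unadjusted rejection about 57%.

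**A milder unadjusted illustration.** Assume one mode enrols everyone the other would, plus extra consenters who drink 20% to 40% more, with 1800 analysed. Share of extras = (p1 − p0) / p1; ratio = 1 + share × (f − 1); SE of the log ratio = sqrt((1/10 + 1) × 4 / 1800) = 0.0494.

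- 50% v 60%: share 0.167, ratios 1.033 and 1.067, rejection 0.102 and 0.257.
- 50% v 55%: share 0.091, ratios 1.018 and 1.036, rejection 0.065 and 0.112.

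These rates, including the 10% to 26%, apply to the non-primary unadjusted model and rest on assumed selection.

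**After adjustment for baseline drinking.** Simulation with no true effect, 903 per group and 400 repetitions. Enrolment is about 60% v 50% on average, and depends on the named factor in one mode only (log-odds per SD in brackets).

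| Selection on | Unadjusted ratio, rejection | Adjusted ratio, rejection |
|---|---|---|
| nothing | 1.00, 4% | 1.00, 4% |
| measured baseline drinking (0.3) | 1.04, 13% | 1.00, 6% |
| underlying drinking trait (0.3) | 1.07, 26% | 1.05, 15% |
| unmeasured prognosis (0.3) | 1.03, 10% | 1.03, 9% |
| unmeasured prognosis (0.5) | 1.05, 17% | 1.05, 20% |

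With 400 repetitions, the Monte Carlo standard error is 1 to 2 percentage points. The simulation adjusts for baseline drinking only, not the other planned covariates, and does not model the eligibility cut.

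**The case against.** The strongest reply has four parts.

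1. The adjusted model is already primary and carries baseline drinking, demographic items and the motivational ratings. This stands, and it removes selection on what those items measure. It does not reach unmeasured factors.
2. Nothing in the protocol fixes the size of selection, or says that it relates to drinking. The information on group allocation was the same in both consent modes. This stands too. A reader might infer that confirming hypothesis 3 would by itself invalidate hypothesis 6. It would not, because the selection must also relate to drinking or prognosis.
3. Hypothesis 6 is labelled exploratory and worded as a difference, and Limitations calls the substudies unpowered. A reader might infer that the protocol asserts a causal effect of consent mode on drinking. It does not; it leaves that reading open. But the limitation stated concerns precision, and selection bias does not shrink with more participants.
4. The intention-to-treat sentence may have been meant for trial participants only, since follow-up times and the 2126 count from the main allocation. That is possible, but the sentence says all analyses, and the protocol also uses the word randomized for consent mode.

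A reader might also object that the stated hypothesis 6 model has no term for the main allocation. That is not a defect of this kind. The main allocation is randomized separately after enrolment, so omitting it causes no bias. Mixing means of 10 and 8.5 adds 0.75² = 0.56 to a variance of about 9.25 + 9.25² = 95, or 0.6%.

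**Conclusion.** The all-randomized statement is wrong as written for hypothesis 6. That follows from the order of events alone and needs no numerical assumption.

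The possible bias is a separate matter, of unknown size. It requires selection by consent mode that relates to drinking or prognosis and is not captured by the adjusted model. Under the selection assumed above, adjusted ratios ran from 1.00 to 1.05, and a nominal 5% test rejected about 6% to 20% of the time. These figures illustrate and do not predict.

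The point is minor: it concerns the interpretation of one exploratory hypothesis. A reader might infer a threat to the main trial result, but the intervention/control and Info-1/Info-2 allocations follow consent and eligibility, so hypotheses 1 and 7 are unaffected.

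**What to change.** - In Statistical Analysis Methods, keep the all-randomized statement for the intervention/control and Info-1/Info-2 allocations. For consent mode, limit it to the enrolment outcome of hypothesis 3.
- State that hypothesis 6 is conditional on enrolment, rests on the adjusted model, and will be reported as an association among enrolled participants rather than as a randomized effect of consent mode.
- Interpret it beside the enrolment rates by consent mode, which are already planned, and the baseline drinking of enrolled participants by consent mode. The planned baseline comparisons among groups may already supply the latter.

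The cost is a few sentences and a slightly weaker claim for one exploratory hypothesis. No new data are needed.

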### Follow-Up Attempts

There are 3 follow-up stages: 1, 2, and 4 months after randomization. All follow-ups will be initiated by sending SMS messages to participants with hyperlinks to questionnaires. In all cases, the following attempts will be made to collect data from nonresponders:

A total of 2 reminders will be sent 2 days apart to those who have not responded.If no response is given to (1), then we will send questions directly in an SMS message, asking participants to respond directly with an SMS (no hyperlink).At 1 month, we will ask all 3 mediator questions.At 2 and 4 months, we will only ask for primary alcohol outcome measures.If there is no response given to (2), we will attempt to call participants to collect responses to the same questions as in (2). A maximum of 5 attempts will be made.

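### The 2-month SMS and phone fallback omits the three mediators, so the 2-to-4-month half of main hypothesis 2 rests only on web-questionnaire respondents

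*Protocol article*

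**What the plan says.** In the Hypotheses textbox, main hypothesis 2 has two halves. In the first, confidence, importance and know-how at 1 month mediate the effect on drinking at 2 months. The second reads: "The same measures at 2-month follow-up will mediate the effect on drinking outcomes at 4-month follow-up".

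The Measures section confirms that the items are asked at the later time points, in adapted form: "The wording of the questions at 2- and 4-month follow-up will change to include those who have reduced their consumption".

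The Follow-Up Attempts section sets out how nonresponders are pursued. After the web link, "A total of 2 reminders will be sent 2 days apart to those who have not responded". The next step is a direct SMS without a link. Its content differs by time point. For the first follow-up, "At 1 month, we will ask all 3 mediator questions". For the later ones, "At 2 and 4 months, we will only ask for primary alcohol outcome measures". The last step, up to five phone calls, asks the same questions as the SMS.

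Under Statistical Analysis Methods, the protocol discusses systematic missingness and says "it may be the case that early responders differ from late responders", adding that late responders may be closer to nonresponders. It plans to check this by regressing the primary outcomes on the number of contact attempts.

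**The concern.** The first half of hypothesis 2 has its mediators collected in every mode of contact. The second half has them collected by web only. Participants reached at 2 months by direct SMS or phone supply a 2-month alcohol outcome, and may supply a 4-month one, but drop out of the 2-to-4-month mediation analysis because the mediator was never asked.

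Two things are at stake. The first is selection. How a person responds is determined after randomization. The intervention arm receives weekly SMS links to a dashboard, and a person's confidence or sense of importance could affect whether they answer a web link. If so, the allocation-to-mediator path is estimated in a selected group. The second is precision, in an analysis that is both a main hypothesis and one of the key objectives listed under Aims. No analysis plan can recover answers that were never requested.

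**Working it through.** **Step 1. What is collected, by mode and time** (Follow-Up, Measures and Follow-Up Attempts sections)

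| Follow-up | Web questionnaire | Direct SMS and phone | Role in hypothesis 2 |
|---|---|---|---|
| 1 month | three mediators | three mediators | mediators for the 2-month outcome |
| 2 months | alcohol, three mediators, recall | primary alcohol outcomes | mediators for the 4-month outcome |
| 4 months | alcohol, three mediators, experience items | primary alcohol outcomes | outcome for the 2-month mediators |

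The gap is the 2-month fallback cell. The 4-month fallback cell creates no gap, because no part of hypothesis 2 uses mediators measured at 4 months.

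The planned check on contact attempts cannot fill the gap. For the 2-month mediators, the only observable levels are the first link and the two reminders; beyond that there are no mediator data.

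**Step 2. The plan's own figures.** Simple inflation gives 1800 / 0.85 = 2118. Simulating 1800/r − 1800 with r from a beta distribution (mean 0.85, SD 0.05) gives a mean loss of 325 and an interquartile range of 231 to 398. The protocol states 326 (231, 398) and 2126 randomized. The figures reproduce and are not in dispute, so 2126 is used below.

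**Step 3. How many would have a 2-month mediator.** The 85% is the protocol's assumption for 4 months, where it expects response to be lowest; it is applied here to 2 months as well. The share w of responders who answer by web is not given, so a range is assumed.

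Responders by any mode: 2126 × 0.85 = 1807.

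With a 2-month mediator: 1807 × w.

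| Assumed w | Number with mediator | Share of 2126 | SE ratio 1/√w |
|---|---|---|---|
| 0.40 | 723 | 34% | 1.58 |
| 0.60 | 1084 | 51% | 1.29 |
| 0.80 | 1446 | 68% | 1.12 |

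The SE ratio compares 1807w with 1807 at the same residual variation: √(1807 / 1807w) = 1/√w. It does not depend on the 85%.

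**Step 4. Why these ratios are upper bounds for each w.** Let q be the share of fallback respondents who would answer the mediator items if asked. Let p₁ and p₂ be the chances of a 4-month outcome among web and fallback respondents. With the items added, the usable sample grows by the factor

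(w·p₁ + (1 − w)·q·p₂) / (w·p₁).

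This equals 1/w only if q = 1 and p₁ = p₂. It is smaller if some fallback respondents skip the items, or if they are less likely to answer at 4 months. As an illustration with w = 0.60, q = 0.5 (assumed) and p₁ = p₂, the factor is (0.60 + 0.40 × 0.5) / 0.60 = 1.33, so the SE ratio is √1.33 = 1.15 rather than 1.29.

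**Step 5. Bias.** Its size would require the relation between response mode, mediator and outcome in each arm. The document gives none of these, so no figure can be put on it.

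**The case against.** The strongest reply is that this is a deliberate trade-off. The Follow-Up section describes the 1-month questionnaire as the one for mediators and the later ones as being about alcohol. The fallback at each stage asks only for that stage's main content; the 2-month recall items are dropped under the same rule. Two months is the primary time point, and a longer message could cost replies on the primary outcome. That risk is real, although the protocol states neither this reason nor the consequence for hypothesis 2. It is largely met by asking for the mediators only after the alcohol answers are in hand.

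It can also be said that the affected part is narrow, that the mediators are described as explored, and that no power is claimed for mediation. This stands and limits the weight of the point. The Limitations section's description of work as preliminary, however, refers to the three substudies, and mediation is not one of them.

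Missing mediators could be imputed in an analysis plan not shown here, using baseline and 1-month mediators and 2-month drinking. That is possible, and silence on it is no fault. Such imputation would still rest on web respondents alone for the 2-month values.

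Three stronger readings are tempting but not supported:

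- A reader might infer that the mediation analysis breaks down a total effect estimated in a different, larger sample. The Hypothesis 2 analysis section does not say so; total, direct and indirect effects could all be estimated among people with both mediator and outcome.
- A reader might take the web group to be only prompt responders. It includes those who answer after the second reminder.
- A reader might take the protocol to assert that late responders differ. It raises this only as a possibility to be checked.

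**Conclusion.** The point holds as a gap in data collection: the 2-month mediators are required by the second half of a main hypothesis and are not requested from anyone reached only by SMS or phone at that time. It follows from the text alone and needs no assumed figure.

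Its consequences are limited. The primary 2-month effect, the 4-month effect and the 1-to-2-month mediation are untouched. Selection bias in the 2-to-4-month mediation is plausible but neither shown nor quantifiable. The loss of precision is at most a factor of about 1.58, 1.29 or 1.12 in the standard error for web shares of 40%, 60% or 80%. Those shares are assumptions, and the factors presume complete answers from everyone in the fallback and 4-month response no higher among them than among web respondents. They should not be read as estimates of the actual loss. This is a cheap improvement that should be made, not a threat to the trial's main conclusion.

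**What to change.** In the Follow-Up Attempts section, extend the 2-month fallback to include the confidence, importance and know-how items in their 2-month wording. Ask them only after the primary alcohol outcomes have been recorded: at the end of the phone call, or in a second SMS sent once the alcohol reply has arrived. A participant who stops there has still given the primary outcome. Leave the 4-month fallback unchanged.

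The cost is three short questions for late responders at one time point, with slight extra burden and some partial replies. The 1-month fallback already uses the same three items by SMS and phone, so no new method is needed. The change has to be in place before 2-month follow-up, since mediators not collected then cannot be obtained later.

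If the fallback is left as it is, the protocol should say that the 2-to-4-month mediation analysis is confined to 2-month web respondents.
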